## Results

The motion-based technology intervention has the potential to positively impact participants’ physical function, specifically balance (as measured through the Mini-BESTest) and movement confidence (analyzed from coded video recordings). This could confirm the feasibility and potential benefits of using motion-based technology to deliver exercise interventions to people with dementia or MCI. There is also potential for the motion-based technology intervention to positively impact the cognitive function of people with dementia or MCI (as measured through MoCA score), offering new approaches for cognitive rehabilitation with this population. The project was funded in 2019 and enrollment was completed on February 28, 2020. Data analysis is underway and the first results are expected to be submitted for publication in 2021.

## Discussion

### Principal Findings

This study is designed to examine the impacts of a group motion-based technology intervention on balance, movement confidence, and cognitive function among people with dementia or MCI. To our knowledge, this is the first study in an emerging body of literature to investigate these important outcomes with regard to the use of motion-based technology for people with dementia or MCI.

### Limitations

Despite the suggested contributions of the study, the proposed study features several potential limitations. First, there is a high risk of researcher bias given that the first author (ED) will be the one to conduct all pre- and posttest measures (ie, MoCA and Mini-BESTest), facilitate the study intervention with participants, and assist with analyzing participants’ movement confidence data. Thus, we recommend that future intervention studies of this nature be carried out with a larger research team where different members can be responsible for conducting different aspects of the study (ie, 1 person conducts the pre- and posttest measures, 1 person facilitates the intervention, and at least two separate individuals analyze the movement confidence data). However, from an opposite perspective, it could be considered positive that the first author (ED) was involved in all aspects of this preliminary study, in order to comment on feasibility and effectiveness, which can help to inform future studies of a similar nature.

Second, we will recruit participants via self-referral to a study advertisement, which suggests that participants who volunteer to take part in the study may be more keen to improve their balance, movement confidence, and cognitive function, which could influence their willingness to take part in the intervention.

Third, we expect that 40% of recruited participants will not complete the study intervention due to reasons outside of our control (eg, prolonged illness, moving to long-term care).

Fourth, while this study is adequately powered, the sample size is still considered small. However, small sample sizes are common in many rehabilitation studies due to lack of resources, lack of funding, recruitment challenges, and high dropout rates [53].

Fifth, the demographic questionnaire developed for this study does not capture participants’ specific diagnosis (eg, Alzheimer disease) or the number of years since their diagnosis. Indeed, it cannot be ruled out that these demographic variables could impact participants’ level of movement confidence, as well as their ability to improve from the intervention. 

Sixth, we acknowledge that the methods being used to evaluate movement confidence (ie, analysis of coded video recordings) are pilot in nature, meaning that there is a chance that some aspects of movement confidence may not be captured using the proposed approach. We recommend that future studies also include a self-report measure or qualitative methods such as interviews, or both, to capture participants’ true feeling of movement confidence.

Seventh, we will recruit a convenience sample of participants from 4 community-based adult day programs near Toronto, Canada. As such, all study participants will live in the community and come from 1 general geographical location. Thus, the findings of this study may not be generalizable to people living in different geographical locations (eg, rural and remote locations) or people living in different care settings (eg, long-term care homes). Eighth, we acknowledge that the game of bowling is not culturally inclusive and may be familiar only to people from certain cultural backgrounds (eg, North American). As a result, choosing the game of bowling may have the potential to impact the diversity of our study sample, as people who are not familiar with the game may be less likely to take part in the study.

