## Methods

### Study Design

This study will use a standard within-participants design, with measurement at pre- and postintervention (1 group, 2 times).

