### Participants

We will recruit a convenience sample of 24 people with dementia or MCI from 4 community-based adult day programs. The sample size calculation was based on detecting the minimum clinical important difference of 4.0 points [39] on the primary outcome measure (Mini-BESTest) [40], using an effect size of 0.8, an alpha value of .05, a power value of 80%, and a 2-tailed *t* test. We calculated the estimated sample size to be at least 15 participants, which we increased to 24 participants to allow for 40% attrition. We chose an attrition rate of 40% given that absenteeism and unforeseen events (eg, prolonged illness, moving to long-term care) are common among adult day program clients.

Prospective participants will be required to (1) attend the day program at least twice per week on the days in which the intervention is to be offered; (2) meet the screening criteria for the presence of cognitive impairment (determined by a score of ≤25 on the MoCA); (3) speak and understand English well enough to recognize instructions from the facilitator and respond accurately; (4) not have visual impairment that would prevent the participant to view the game screen; (5) be able to stand and walk, with or without an assistive device (eg, walker), to complete the Mini-BESTest; and (6) have the capacity to provide informed consent, or have a substitute decision maker who can provide informed consent. We will exclude participants who do not meet the above criteria from participating in the study.

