### Intervention Description

We will invite participants to take part in a 10-week motion-based technology intervention (Xbox Kinect bowling), held in a group setting at 4 community-based adult day programs. The intervention sessions will take place twice per week for 10 weeks (20 sessions per site). Sessions will be facilitated by the first author (ED) using teaching techniques successfully employed in previous studies involving motion-based technology and people with dementia or MCI, such as verbal prompts, gesture demonstrations, and physical assistance [37]. During each session, approximately six participants will be seated together in a room and will each have a turn to engage with the technology and game. The facilitator will call upon each participant in the group 1 at a time to take their turn, which will continue for the duration of each session (approximately 60 minutes). While the active player is engaging with the technology, the rest of the group will sit and observe.

The motion-based technology system to be used in this study is the Xbox One Kinect (Microsoft Corporation). We chose the Xbox One Kinect over other commercially available motion-based technology systems (eg, Nintendo Wii) given that interaction with this system requires no handheld controller and relies purely on naturalistic movements (eg, waving an arm). We will used the commercially available bowling game offered through the Kinect Sports Rivals package in the study, alongside the Xbox One Kinect. We chose the Kinect Sports Rivals bowling game given that the game of bowling is generally familiar.

To partake in the intervention, participants are required to rise from their chair, walk to the line (ie, a piece of black electrical tape placed on the floor in front of the technology to cue participants regarding where to stand), play the bowling game, walk back to the chair, and sit down. We will break down the movements required to play the bowling game for participants in a stepwise manner: (1) raise an arm above the head to activate the Kinect sensor; (2) reach the same arm out to the side; (3) close the hand of the extended arm to pick up a bowling ball; (4) extend the same arm back behind to wind up; (5) open the hand of the same arm to release the ball; and (6) swing the same arm forward to throw the ball.

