### Procedure

We will first ask potential participants to complete the eligibility screening questionnaire and the MoCA [42] to ensure that the study inclusion criteria are met. The MoCA will be conducted in person, in a quiet and private setting (ie, in a separate room) at each day program. The first author (ED) will be responsible for administering and scoring the MoCA. At this time, prospective participants will also rereview the informed consent with the researcher, who will then determine their capacity to provide informed consent using the decision-making ability and capacity-probing questions. Once a participant has reviewed the informed consent form to their satisfaction, they will be asked to sign the informed consent form in the presence of the researcher, provided that they have the capacity to independently provide informed consent. Given that decisions are time specific, we will review each participants’ capacity to consent on an ongoing basis (ie, at each point of interaction). All consent and assent forms will be signed in a quiet and private area at the day program.

Upon providing informed consent (whether through independent consent or substitute decision-maker consent plus participant assent), each participant will complete the demographic questionnaire and the Mini-BESTest [40]. We will complete the pretest measurements as close to the eligibility measurements and to the intervention as possible (ie, within 1-3 days) to ensure that the MoCA (used for eligibility and outcome purposes) and Mini-BESTest scores do not become outdated. We will conduct the Mini-BESTest in an open area (eg, exercise room) at each day program to ensure that there is enough space to perform the test. Additionally, 2 members of the research team will be present during the Mini-BESTest to ensure that participants can safely perform the test. That is, 1 research team member will evaluate the participants’ performance while the other member acts as a spotter.

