Video recordings will be coded by 4 independent raters, 1 of whom is the first author (ED). Prior to formally coding the videos for analysis, each rater will undergo training using the Observer XT video analysis software [51] and the movement confidence coding scheme. This will involve completing an introductory coding exercise, reviewing the video-recorded data, familiarizing themselves with the coding scheme and its operational definitions, and practicing coding the videos. We will compare the practice work of each coder for consistency using interrater reliability analysis to determine whether the 4 raters are reliably evaluating the same material [52]. This will also reduce the likelihood of researcher bias, given that the work of the other 3 raters will be compared for consistency against that of the fourth rater (ED), who is also involved in facilitating the study intervention and conducting the pretest and posttest measures. Once interrater reliability between the 4 raters reaches at least 80% agreement, the 4 raters will formally code the video recordings for analysis. This involves dividing up the coding so that each rater will be responsible for coding 1 of the 4 study sites (ie, 6 sessions per rater).

We will analyze all 6 video recordings from each data collection site. These comprise recordings of the first 2 sessions (1 and 2), the middle 2 sessions (11 and 12), and the final 2 sessions (19 and 20). Each rater will code the entirety of each selected session (60 minutes), with each bowling turn of each participant analyzed. Then, we will combine coded data from the 6 sessions into 3 respective time points: start (T1) = the first 2 sessions, midpoint (T2) = the 2 middle sessions, and end (T3) = the last 2 sessions.

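### The facilitator conducts every pre- and posttest measure and codes one video site alone; the practice agreement check does not cure this, and the existing raters could reduce it for the video outcome

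*Protocol article*

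**What the plan says.** All references are to the protocol article.

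- **Design (Study Design).** A "standard within-participants design, with measurement at pre- and postintervention (1 group, 2 times"), with no comparison arm.
- **Delivery (Intervention Description).** "Sessions will be facilitated by the first author".
- **Assessment (Limitations, Procedure).** The same person will "conduct all pre- and posttest measures (ie, MoCA and Mini-BESTest), facilitate the study intervention with participants, and assist with analyzing" the movement confidence data, and also administers and scores the MoCA.
- **Staff at the primary outcome (Procedure).** "2 members of the research team will be present during the Mini-BESTest": one evaluates and the other spots for safety.
- **Video coding (Analysis of Video-Recorded Data).** There are four raters, one of them the facilitator. They train, and their practice coding is compared until agreement reaches at least 80%. The article presents this comparison as a way to lower researcher bias. Formal coding then proceeds by "dividing up the coding so that each rater will be responsible for coding 1 of the 4 study sites (ie, 6 sessions per rater"). Sessions 1 and 2 form T1, 11 and 12 form T2, and 19 and 20 form T3.
- **Disclosure (Limitations).** The overlap of roles is listed first and rated a high risk. Separating the roles is left to later studies with more staff.
- **Sample size (Participants).** The target for the Mini-BESTest is a "minimum clinical important difference of 4.0 points". The other inputs are a standardized effect of 0.8, two-sided alpha .05 and 80% power. From these the article concludes: "We calculated the estimated sample size to be at least 15 participants, which we increased to 24 participants to allow for 40% attrition".

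**The concern.** One person delivers the intervention, conducts the primary outcome assessment before and after it, and codes a quarter of the video. In a controlled trial an assessor's expectation could at least act on both arms. Here the result is the mean posttest score minus the mean pretest score, so any systematic generosity at posttest is indistinguishable from benefit.

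Two statements in the article make this more than a disclosed limitation. The video section offers the rater comparison as a safeguard, although its reach is short. The Limitations section treats separation of roles as something for a bigger team, although the Procedure and video sections already show a second person at each Mini-BESTest and three raters besides the facilitator. At stake are Hypothesis 1 (balance) and Hypothesis 2 (movement confidence). Hypothesis 3 (MoCA) is exposed in the same way.

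**Working it through.** **1. Reproduce the plan's own figure.** For a paired two-sided t test, T follows a noncentral t with n − 1 degrees of freedom and noncentrality d√n, and rejection occurs when |T| > t(.975, n − 1). With d = 0.8 and alpha .05, power is 79.0% at n = 14 and 82.1% at n = 15, so the stated minimum of 15 is correct. For attrition, 15/(1 − 0.4) = 25, against the stated 24 (24 × 0.6 = 14.4 completers). The difference is negligible here.

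**2. Derive the spread.** The article gives no SD of change. Its target and effect size imply SD = 4.0/0.8 = 5.0 points.

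**3. Smallest mean change that reaches P < .05:** t(.975, n − 1) × 5.0/√n.
- n = 15: 2.145 × 5.0/3.873 = 2.77 points.
- n = 24: 2.069 × 5.0/4.899 = 2.11 points.

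Both lie below the 4.0-point target difference.

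**4. Effect of a posttest scoring shift.** Set the true change to 0 and let scoring add b points at posttest. The observed mean change is then centred on b, and the rejection rate is the power formula with d = b/5.0. The values of b are assumptions, because the article gives no size for the bias.

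| Shift b (points) | d = b/5.0 | Significant, n = 15 | Significant, n = 24 |
|---|---|---|---|
| 0 | 0 | 5% | 5% |
| 0.5 | 0.1 | 6.5% | 7.6% |
| 1 | 0.2 | 11.2% | 15.6% |
| 2 | 0.4 | 30.3% | 46.7% |
| 3 | 0.6 | 58.0% | 80.4% |

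The n = 24 column treats every recruited participant as fully observed, and n = 15 is the planned evaluable number. The planned model also carries site and sessions attended as covariates and uses multiple imputation, so the simple t test is an illustration.

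**5. What the agreement check covers.** Set against the three outcomes:
- Mini-BESTest: not covered.
- MoCA: not covered.
- Video: practice coding only. In the formal phase each site has a single rater and no double coding is described. Agreement is judged against the rater who also facilitates and tests, so it can carry that rater's expectations to the others.

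**6. What the existing raters could take over.** Coded sessions: 4 sites × 6 = 24. The facilitator's share is 6/24 = 25%. Spread over three raters, the load is 24/3 = 8 sessions' worth each instead of 6, an increase of 2/6, or one third.

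**The case against.** The strongest reply is that the authors already say all this. Limitations names the three overlapping roles, rates the risk high and recommends separating them. That stands: the overlap itself is disclosed and not misstated. What is left is the overstated safeguard in the video section and the remedies open to this study.

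Four stronger readings are tempting, and the documents do not support them.

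- *That staff already on the study could remove most of the bias.* Nothing in the article sizes the bias, so no share can be computed. In a one-group pre-post study any live assessor knows which visit is the posttest. Withholding the pretest sheet hides the earlier score, not the time point. Only intervention sessions are described as filmed, so the Mini-BESTest cannot be rescored masked from the recordings described. Nor does the article say that the spotter is trained to score.
- *That leniency on three Mini-BESTest items would by itself make Hypothesis 1 significant.* A 3-point shift is a shift in the expected mean and gives significance in 58% to 80% of trials. The article gives 14 items and 28 points but not the scoring steps, so equating one item upgrade with one point is a further assumption.
- *That no rater is masked.* For the facilitator this follows from the role. For the other three it rests on the silence of a condensed article, and clip handling may be set out elsewhere.
- *That the agreement check is worthless.* Comparing four trained raters on operational definitions can expose an idiosyncratic coder. Its fault is limited reach.

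Timing also counts. Results reports that enrollment was completed on February 28, 2020 and that analysis is underway, so changing the Mini-BESTest assessor may no longer be possible. What then remains concerns an outcome method that the authors themselves describe as a pilot.

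**Conclusion.** The point holds in a limited form. One person leads the sessions, conducts all pre- and posttest measures and codes 25% of the recorded sessions, and cannot be masked to the time point of those sessions. The statement that comparing raters with this person lowers researcher bias claims more than a practice-coding check can deliver. The deferral to a bigger team is only partly justified, because three other raters are already in place for the video.

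The possible size on the primary outcome, given no true change and the implied SD of 5.0, is a false-positive rate of about 11% to 16% for a 1-point shift, 30% to 47% for 2 points and 58% to 80% for 3 points, against a nominal 5%. These figures show sensitivity to an assumed shift and are not evidence that one occurred. The proposed change reduces the bias by an unknown amount, chiefly in the video outcome, and leaves sample size, alpha and power as they are.

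**What to change.** 1. **Formal video coding.** Take the facilitator off it. Split that site by participant among the other three raters (about six participants, so two each, across all six sessions), so that the rater stays constant within participant and does not mix with time.
2. **Clip order.** Strip session number and date from the clips, and code each participant's clips in random order across T1 to T3. State that visible skill may still reveal the week.
3. **Wording.** In Analysis of Video-Recorded Data, limit the bias claim to consistency of practice coding, and say that it does not extend to the Mini-BESTest or MoCA.
4. **Mini-BESTest, only if testing is not finished.** Have a trained team member other than the facilitator score both visits with pretest scores withheld, keeping two people present as now. This removes the facilitator's stake but not knowledge of the time point. If testing is finished, say so and keep the limitation.

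The article describes no second person at the MoCA, so this change leaves Hypothesis 3 as it stands.

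**Cost.** About one third more coding for three raters (8 rather than 6 sessions' worth each) plus clip preparation. Items 1 and 2 act on existing recordings and may still be possible. Item 3 costs nothing. Item 4 needs scoring training, whose cost the article does not let one judge.

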### Comparison With Prior Work

The findings of the proposed study can contribute to the literature in several regards. First, the results of this study could provide further insight into the potential impacts of motion-based technology for people with dementia or MCI, which could stimulate further outcomes-based research in this area. Second, this work can be used to inform the development and design of motion-based technology games for people with dementia or MCI. To date, commercially available motion-based technology games have not been targeted toward people with dementia or MCI, which likely plays a role in the lack of rehabilitation literature regarding the impacts of motion-based technology interventions for this population [38]. Indeed, there is a need for further research using motion-based technology systems and games that are specifically designed to be enjoyable and accessible for this population [28]. For example, systems could be developed that provide in-game prompts, thus reducing the demands on an external (eg, human) facilitator. Similarly, errorless learning capabilities among people with dementia or MCI [54] could be leveraged within motion-based technology games by creating a wider repertoire of games that can be broken down into procedural steps.

Broadly, we expect that this research will be relevant to scientific, clinical, and professional audiences. For example, we expect that this research will be relevant to scholarly rehabilitation practice, advocacy, or advancing understanding of occupation (ie, meaningful activity) as a fundamental social determinant of health and well-being for people with dementia or MCI. Understanding the potential impacts of using motion-based technology with people with dementia or MCI can inform future evidence-based, community-based rehabilitation practice. That is, if participants show significant improvements in balance, movement confidence, and cognitive function as a result of partaking in the motion-based technology intervention, there is the potential of motion-based technology systems being incorporated into rehabilitation interventions targeting these outcomes. Additionally, we expect that this study will demonstrate the feasibility of using motion-based technology to deliver task-specific interventions to people with dementia or MCI. This is relevant given that tasks and goals of importance to clients are often used to inform rehabilitation interventions. Finally, this research aims to advocate the inclusion of people with dementia or MCI in rehabilitation science and interventions. We expect that this study will demonstrate the ability of people with dementia or MCI to engage in meaningful activity and emphasize the importance of meaningful activity to support health and well-being of people with dementia or MCI.

